#### Primary endpoint

Change of DAS28-ESR (Disease Activity Score in 28 joints calculated with erythrocyte sedimentation rate) from baseline to 12 Weeks.

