#### Secondary endpoints

Proportion of patients achieving:◦ European Alliance of Associations for Rheumatology (EULAR) moderate or good response◦ DAS28-ESR < 2.6Change in DAS28-CRP (Disease Activity Score in 28 joints calculated with C-reactive protein)Change on ultrasound score (32 joints scored 0-3 for grey scale and power Doppler)Proportion of patients who had a 10% improvement in ultrasound scoreChange in Short Form 36 Health Survey Questionnaire (SF36) resultsChange in Health Assessment Questionnaire (HAQ) resultsChanges in α- and β- diversity of the gut and oral microbiotaChanges in the relative abundance of *Lactobacillus/Limosilactobacillus* and* Bifidobacterium* species in the gutChanges in butyrate-producing species in the gut microbiotaChanges in H2S-producing species in the gut microbiotaChange in the lactulose/mannitol ratioChange in Endotoxemia measured by TLR4 activation in reporter cellsChange in inflammatory biomarkers (C-Reactive Protein, CPR; Erythrocyte sedimentation rate, ESR, faecal calprotectin)Change in serum soluble CD14 (CD14s), lipopolysaccharide-binding protein (LBP), and intestinal fatty acid binding protein levels (IFABP)Change in lipid profile (Triglycerides, Total Cholesterol, HDL and LDL Cholesterol)Change in body composition (Fat Mass, Fat-Free Mass, Total Body Water and Body Cell Mass)Change in anthropometric measurements (body mass index, BMI, and waist circumference)

We will also analyse zonulin levels, serum proteomics, and serum glycomics.

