### Recruitment and eligibility criteria

RA patients diagnosed according to the ACR/EULAR2010 criteria [23], aged 18 years old or older, are invited to participate in this study if eligibility criteria are met at their regular follow-up RA consultations. All participants sign a written informed consent form before any study procedures. Our inclusion criteria are diagnosis duration of at least one year, active disease (DAS28-ESR ≥ 2.6 units), stable medication for at least 12 weeks prior to the baseline assessment (including intra-articular steroid injections), and a low or medium adherence to the MedDiet (defined as a score of < 10 points in the 14-item tool by the PREvención com DIeta MEDiterránea trial, PREDIMED). Patients requiring therapeutic adjustments and/or intra-articular steroid injections during the trial are excluded. Our exclusion criteria are: antibiotic therapy within 4 weeks before enrolment; prednisolone dose > 7.5 mg/day; persistent use of non-steroidal anti-inflammatory drugs: diagnosis of inflammatory or irritable bowel disease, celiac disease, chronic diarrhoea; diagnosis of other immune-mediated or inflammatory diseases; major organ dysfunction; cancer diagnosed in the last five years; presence of health conditions which may impair the ability to consent to study participation (cognitive impairment/psychiatric disease). Regarding the use of antibiotics, although a general recommendation for a washout period is challenging to define, according to literature, a minimum of 4 weeks since cessation of antibiotics is recommended [24] and is considered in this trial. The overall diagram flow of the study is shown in the SPIRIT figure illustrated in Fig. 1. The SPIRIT checklist is provided as supplementary material.

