#### Data management and statistical analysis

Collected data files in paper format are being securely stored in locked filing cabinets within the Nutrition Lab, FMUL, CAML, accessible only to authorized team members. All recorded data and collected samples are coded, and analysis will be performed anonymously. Only members of the research team will have access to data and samples. FMUL has the property of the resulting data and the right to disclose the results as merged data analysis. The Nutrition Lab of FMUL will have access to the final trial dataset and will be responsible for storing conserved data for five years after the last publication.

Statistical analysis will be conducted using SPSS (SPSS® Inc., Chicago, IL) version 28.0 or a subsequent updated version. The Normal data distribution will be verified using the Kolmogorov–Smirnov tests, considering the sample size. Depending on the normality of the data, parametric or non-parametric tests will be used. A *p*-value of less than 0.05 will be considered statistically significant. Descriptive statistics will be used to describe all variables, both by groups (intervention vs. control) and by timing (baseline and final visits). Characteristics between groups at baseline will be compared to identify significant differences that may confound results. To access differences between the baseline and the end of the intervention (paired sample test) as well as between groups (independent samples test), the student's T-Test or its non-parametric equivalent will be used. Multiple regression analysis will be conducted to address the influence of baseline characteristics. An analysis of covariance (ANCOVA) will be carried out when baseline differences need to be controlled, being the group (intervention/control) the independent variable, and the covariates the baseline characteristics and demographic data. To test how the MedDiet + pattern influences the study endpoints, a multivariate analysis of covariance (MANCOVA) will be conducted to assess group differences with multiple dependent variables and adjusting for confounding factors. The existence of a control group allows for statistical comparisons between groups and ensures the true effectiveness of the MedDiet + when adjusting for potential confounders.

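### DAS28-ESR < 2.6 shares its cut with the entry criterion, so baseline DAS28-ESR should always be in its between-arm analysis, a free gain in precision that the named methods do not secure

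*Protocol article*

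**What the plan says.** All places are in the protocol article.

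- **Recruitment and eligibility criteria.** Patients must have "active disease (DAS28-ESR ≥ 2.6 units"), with no margin above that value.
- **Secondary endpoints.** Under "Proportion of patients achieving" the list gives a EULAR moderate or good response and DAS28-ESR below 2.6. A third proportion, the ultrasound responder, appears further down.
- **Primary endpoint.** This is the change in DAS28-ESR "from baseline to 12 Weeks", a continuous outcome.
- **Data management and statistical analysis.** The type of test follows distribution, not outcome type: "Depending on the normality of the data, parametric or non-parametric tests will be used". For differences over time (paired) and between groups (independent samples), the Student's "T-Test or its non-parametric equivalent will be used".
- **Adjustment, same section.** A regression is planned in general terms: "Multiple regression analysis will be conducted to address the influence of baseline characteristics". The covariance model, by contrast, is conditional, as the article states: "An analysis of covariance (ANCOVA) will be carried out when baseline differences need to be controlled". Group is its factor, and the adjustment variables are described only broadly, as "the covariates the baseline characteristics and demographic data". A MANCOVA adjusting for confounders is also planned. Baseline DAS28-ESR is not named.

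**The concern.** Entry and remission meet at the same value. A patient who enters just above 2.6 can cross it through ordinary visit-to-visit variation; one who enters well above it seldom will. Baseline DAS28-ESR therefore carries much of the information about who remits. It is measured in everyone, yet nothing in the plan ensures that it enters the analysis of this endpoint. The methods named are built for continuous outcomes, and ANCOVA depends on baseline differences being judged to need control.

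Two things are at stake. First, an unadjusted comparison gives up power in a trial of 50 per arm that has no formal sample size calculation, and leaves the estimate open to chance imbalance in patients near the cut. Second, since no one is below 2.6 at entry, the proportion below 2.6 can only rise within an arm. A paired before-and-after test of remission would show improvement with no treatment effect at all.

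**Working it through.** The documents give no remission rate, effect size, baseline distribution or SD of change, so there is no figure to reproduce. The check uses these inputs.

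- From the protocol: entry at 2.6 or above, endpoint below 2.6, 50 per arm, significance level 0.05 (two-sided assumed).
- Assumed: baseline normal with mean 3.2, SD 0.8, or mean 3.8, SD 0.9, each truncated at 2.6; 12-week change normal with SD 0.6, 0.8 or 1.0; mean change 0 in control and 0 or -0.5 with the diet.

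**1. How strongly baseline drives remission with no effect.** P(below 2.6) = Φ((2.6 − baseline)/SD of change).

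- From 2.8: Φ(−0.2/0.6), Φ(−0.2/0.8), Φ(−0.2/1.0) = 37%, 40%, 42%.
- From 4.0: Φ(−1.4/0.6), Φ(−1.4/0.8), Φ(−1.4/1.0) = 1%, 4%, 8%.

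The share of patients starting below 3.2 is [Φ((3.2−m)/s) − Φ((2.6−m)/s)] / [1 − Φ((2.6−m)/s)]. For m = 3.2, s = 0.8 this is (0.500 − 0.227)/0.773 = 35%. For m = 3.8, s = 0.9 it is (0.252 − 0.091)/0.909 = 18%. Averaging the crossing probability over the baseline distribution, these patients supply 47% to 79% of no-effect remissions. With wider assumptions (baseline mean up to 4.5, SD 1.0, change SD up to 1.2) the range is 29% to 79%, and baseline alone predicts remission with an AUC of 0.73 to 0.94.

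**2. Effect of chance imbalance on the arm difference.** The SD of the between-arm difference in the number starting below 3.2 is √(2 × 50 × p(1−p)).

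- p = 0.35: √(100 × 0.35 × 0.65) = 4.8 patients, or 4.8/50 = 10 percentage points.
- p = 0.18: √(100 × 0.18 × 0.82) = 3.8 patients, or 8 percentage points.

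A one-SD imbalance moves the remission difference by about 2 to 2.5 points, against an SD of that difference of 5 to 8 points. Imbalance in this group explains 8% to 15% of the variance of the difference; the full baseline value explains 11% to 19%.

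**3. Test size and power.** Simulated trials (3,000 per scenario) compared an unadjusted chi-square test with the score test for arm from logistic regression on arm and baseline DAS28-ESR. Power for an effect of -0.5:

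| Baseline mean (SD) | Change SD | Chi-square | Adjusted score test | Gain (points) |
|---|---|---|---|---|
| 3.2 (0.8) | 0.6 | 61% | 73% | 12 |
| 3.2 (0.8) | 0.8 | 48% | 56% | 8 |
| 3.2 (0.8) | 1.0 | 37% | 42% | 5 |
| 3.8 (0.9) | 0.6 | 42% | 54% | 12 |
| 3.8 (0.9) | 0.8 | 36% | 42% | 6 |
| 3.8 (0.9) | 1.0 | 30% | 34% | 4 |

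With no effect, the score test rejected in 4% to 6% of trials and chi-square in 4.4% to 6.2%. The choice of test matters: under related assumptions (change SD 0.9) the likelihood-ratio test from the same model rejected in 6.6% to 8.6%.

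**4. A paired test within one arm.** Baseline remission is zero, so with k remitters at week 12 the exact paired p-value is 2 × 0.5^k. Five give 2/32 = 0.063 and six give 2/64 = 0.031, so six of 50 are enough. With no effect, simulation gave such a result in 16% to 98% of control arms over the six scenarios.

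**The case against.** The strongest reply is that nothing here is biased. Arms are randomised 50:50, so patients near 2.6 are balanced in expectation, and the unadjusted test keeps its size near 5%. This stands. A reader might infer from the shared cut that the remission comparison mainly reflects who started near 2.6. The documents do not support that. It may describe who remits within an arm, and even there the share is 29% to 79% depending on assumptions. For the difference between arms, more than 80% of the variance has nothing to do with baseline.

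Nor is adjustment absent: regression on baseline characteristics is planned, and baseline DAS28-ESR falls naturally among them. That also stands. The gap is that this covariate is not named and that ANCOVA is conditional.

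A third reply is that the article is condensed and that the test for a proportion is normally left to an analysis plan, which is not shown. Taken alone, the missing binary method is indeed no finding. The article also does not name a chi-square test, so the comparator above is an assumed fallback, and it does not say that the paired test will be applied to remission.

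Finally, the gain is modest and rests on assumed inputs. An unadjusted Fisher test has lower power still (21% to 53%), but that extra gap comes from Fisher's conservatism and should not be credited to the covariate.

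**Conclusion.** The point holds as a free improvement to a secondary analysis. It does not show an error that invalidates the comparison. The shared cut makes baseline DAS28-ESR a strong predictor of remission and fixes baseline remission at 0%; the plan neither names that covariate nor makes ANCOVA unconditional. The cost is precision and exposure to chance imbalance, not bias.

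For DAS28-ESR < 2.6, always adjusting adds about 4 to 12 percentage points of power over an unadjusted chi-square test, with size essentially unchanged. This assumes normal changes with SD 0.6 to 1.0, an effect of -0.5, 50 per arm with no dropout, and the two baseline distributions above. No gain was computed for EULAR response or the ultrasound responder, and the shared-cut argument does not reach them.

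**What to change.** Add a sentence to the analysis section, or to the analysis plan if there is one:

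- Analyse DAS28-ESR < 2.6, and by the same approach EULAR response, by logistic regression on arm with baseline DAS28-ESR as a continuous covariate that is always included, whatever the observed baseline differences.
- Test arm with the score test.
- Report the baseline-standardised risk difference with its 95% CI: predict each participant's probability under both arms, average over all participants, and subtract.
- Interpret remission only between arms, with no paired within-arm test.

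The cost is the wording. The covariate is already collected on everyone at baseline, standard software can do the analysis, and no visit, criterion or procedure changes. The choice should be fixed before outcome data are examined by arm.

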## Methods

### Study design, setting and aims

This is a single-centre randomised controlled trial, coordinated and implemented at Faculdade de Medicina, Universidade de Lisboa (FMUL), Gulbenkian Institute for Molecular Medicine (GIMM) and Unidade Local de Saúde (ULS) Santa Maria, Centro Académico de Medicina de Lisboa (CAML), Lisbon, Portugal. This trial is registered in ClinicalTrials.gov (NCT06758817; date of registry: January 6th 2025). This trial was approved by the ethics committee of CAML (Ref. Nº114/22).

We aim to investigate whether a nutritional intervention based on a MedDiet enriched with fermented foods (MedDiet +) may influence disease activity, functional status, quality of life, intestinal permeability, endotoxemia, inflammatory biomarkers, intestinal and oral microbiota, serum proteomics and serum glycome.

The first participant was enrolled in July 2023, and data collection is anticipated to conclude by the end of 2025. Currently, the effect of the MedDiet on the Disease Activity Score in 28 joints (DAS28) of RA patients is not yet known, making it unfeasible to conduct a formal sample size calculation. Considering the number of potentially eligible RA patients treated at the Rheumatology Department at ULS Santa Maria, our recruitment capacity, available funding, and the size of recent published studies in this area, a convenience sample of 100 participants will be recruited.

Patients meeting eligibility criteria are randomly assigned to the intervention MedDiet + (*n* = 50) or control (*n* = 50) groups through an online block randomisation generator. Due to the nature of the trial, the participants and the registered dietitians responsible for implementing the study are not blinded. However, the clinicians evaluating the clinical outcome measures and the researchers performing the laboratory tests are blinded.

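### The method for the primary endpoint is chosen from the observed data, and adjustment for baseline DAS28-ESR is conditional rather than assured

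*Protocol article*

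**What the plan says.** The primary endpoint (Primary endpoint) is "Change of DAS28-ESR (Disease Activity Score in 28 joints calculated with erythrocyte sedimentation rate) from baseline to 12 Weeks". How it will be analysed is set out in one place, Data management and statistical analysis, as a series of conditional steps:

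- Normality is checked by Kolmogorov-Smirnov tests, and then "Depending on the normality of the data, parametric or non-parametric tests will be used".
- The arms are compared at baseline: "Characteristics between groups at baseline will be compared to identify significant differences that may confound results".
- The between-group comparison is an independent-samples t-test or its rank equivalent.
- "An analysis of covariance (ANCOVA) will be carried out when baseline differences need to be controlled". Its covariates are described only generically, as baseline and demographic variables.
- Multiple regression on baseline characteristics and a MANCOVA across endpoints are listed without that condition. Their covariates are not listed either.

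The significance threshold is a p-"value of less than 0.05 will be considered statistically significant". On size, Study design, setting and aims says "a convenience sample of 100 participants will be recruited", randomised 50 to each arm in blocks. It explains that the unknown effect of the diet on DAS28 was "making it unfeasible to conduct a formal sample size calculation".

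**The concern.** Two choices that shape the primary result are left to the data.

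The first is adjustment. Allocation is randomised, so any baseline difference arises by chance. A significance test of that difference tests a null hypothesis already known to be true, and it says nothing about whether the variable predicts outcome. Baseline DAS28-ESR is measured in everyone and can be expected to predict the week-12 value. Whether to adjust for it should not depend on how the arms happen to differ.

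The second is the test. A t-test estimates a difference in means; a rank test compares distributions. A normality gate lets the sample decide which question is answered. With about 50 per arm, a comparison of means does not need that gate.

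Precision matters here because the sample was set by feasibility. With 50 per arm, two-sided 5% and 80% power, the detectable difference is about 0.56 SD of the analysed variable.

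**Working it through.** **Inputs.** From the article: 50 per arm, a 5% level (two-sided assumed), the change endpoint, and entry at DAS28-ESR of at least 2.6. Not in the article, so assumed: the baseline to week-12 correlation r (0.3 to 0.7) and the ratio k of the week-12 SD to the baseline SD. There is no power calculation to reproduce.

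**Precision.** With the baseline SD set to 1:

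- Var(change) ∝ 1 + k² − 2rk
- Var(ANCOVA) ∝ k²(1 − r²)
- The difference between the two is (1 − rk)², which is never negative.

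With k = 1 the ratio ANCOVA/change is (1 − r²)/(2(1 − r)) = (1 + r)/2.

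| r | k | Variance ratio | 100 patients act like |
|---|---|---|---|
| 0.3 | 1.0 | 0.65 | 100/0.65 = 154 |
| 0.5 | 1.0 | 0.75 | 133 |
| 0.7 | 1.0 | 0.85 | 118 |
| 0.5 | 1.2 | 1.08/1.24 = 0.87 | 115 |
| 0.6 | 1.3 | 1.082/1.13 = 0.96 | 104 |

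**What the conditional rule recovers.** If the trigger is p < 0.05 on baseline DAS28-ESR, it fires in about 5% of trials. The simulation used 100,000 trials per setting, bivariate normal data, k = 1 and an illustrative effect of 0.5 baseline SD:

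| r | Power, change score only | Power, conditional rule | Power, always ANCOVA |
|---|---|---|---|
| 0.3 | 55% | 57% | 74% |
| 0.5 | 70% | 70% | 81% |
| 0.7 | 89% | 90% | 93% |

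**Imbalance below the trigger.** The largest non-significant imbalance is t(0.975, 98) × √(2/50) = 1.984 × 0.2 = 0.40 SD. An imbalance of d shifts the change-score estimate by (1 − rk)d. For d = 0.3 SD (p = 0.14) and k = 1 the shift is 0.21, 0.15 and 0.09 SD at r = 0.3, 0.5 and 0.7. At r = 0.6 and k = 1.3 it is 0.22 × 0.3 = 0.07 SD. In the simulation about 16% of trials had an imbalance above 0.25 SD that was still non-significant. Within those trials the change-score test rejected a true null in 10.0%, 8.7% and 7.3% (r = 0.3, 0.5, 0.7). ANCOVA rejected in 4.9% to 5.1%.

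**Overall type I error.** The conditional rule gave 4.0% to 4.6%. The normality-gated test gave 4.0% to 5.3% over normal, skewed and heavy-tailed data (3,000 trials per setting).

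**How often the gate changes the test.** With exactly normal data and a 5% test in each arm, the expected rate is 1 − 0.95² = 9.75% (about 9% in simulation). One pooled test would give 5%. With moderately heavy-tailed or skewed data, the gate flagged 37% and 66% of trials.

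**Screening many variables.** If k′ independent characteristics are each tested at 5%, at least one is significant with probability 1 − 0.95^k′: 40% for 10 and 64% for 20.

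**The case against.** The strongest defence has five parts.

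- **The trigger is not a stated p-value rule.** A reader might infer that ANCOVA follows only from a significant baseline test. That reading joins two sentences; the ANCOVA sentence gives no threshold. This stands: the trigger is apparent, not stated. A looser trigger leaves more discretion, not less.
- **Adjusted results will exist.** A reader might infer that chance imbalance goes wholly uncorrected, or that the unadjusted t-test is the declared primary analysis. Neither is supported. Regression and MANCOVA are listed unconditionally, and no test is labelled primary or default. But without fixed covariates or status, these analyses add candidates rather than settle the choice.
- **The 5% trigger rate is for DAS28-ESR alone.** If any screened variable can trigger ANCOVA, it could run much more often. This stands, but it is not stated that baseline DAS28-ESR would then be in the model.
- **The precision gain rests on equal SDs.** The entry threshold truncates baseline DAS28-ESR but not the week-12 value, so a larger week-12 SD is plausible and the gain would be smaller. This stands and is shown in the first table.
- **A condensed article may leave the model to an SAP.** This is fair for covariate lists. It does not cover the gate and the condition on ANCOVA, which the article states outright; an SAP that implemented them faithfully would carry the same weakness.

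**Conclusion.** The point holds as a should-fix. The article makes both the type of test and the use of ANCOVA depend on observed data, and it does not assure adjustment for baseline DAS28-ESR.

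A reader might go further and infer inflated false-positive risk. The calculations do not support that: each rule, followed mechanically, stays close to or below 5% overall, and under randomisation the t-test on change is valid and unbiased across trials. The harm is narrower:

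- lost precision: a variance ratio of 0.65 to 0.85 for r from 0.3 to 0.7 with equal SDs, but 0.87 to 0.96 in the two examples with a larger week-12 SD;
- a shifted estimate in the minority of trials where a sizeable chance imbalance does not trigger adjustment;
- a mean or rank target that is not fixed in advance.

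The direction does not depend on the assumed r and k, since in large samples ANCOVA is never less precise than the change score. The size does, and the article gives neither value. The 9% to 10% gate rate under normality assumes testing in each arm, which the article does not specify.

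**What to change.** Before any unblinded analysis, name one primary analysis: a linear model of week-12 DAS28-ESR on randomised group, with baseline DAS28-ESR always included and any further covariates listed in advance. Report the adjusted mean difference with its 95% confidence interval and p-value. Fitting change instead of the week-12 value gives the same group effect once baseline is in the model, so the endpoint need not be redefined.

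Describe baseline characteristics by arm, but drop their significance tests and the normality test as selectors of the method. Keep a rank-based or bootstrap analysis as a stated sensitivity analysis. Say that the regression and MANCOVA analyses are supportive.

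Adjusting the other continuous endpoints for their own baseline values is a reasonable option, not part of the required change.

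The cost is a dated change of wording in the analysis plan. No new data, visits or patients are needed, because DAS28-ESR is already collected at both time points in both arms.
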